### Specific Objectives

To evaluate and compare the effects of 12 weeks of combined training with different weekly frequencies on the following outcomes in middle-aged and older individuals with hypertension:

*Primary outcomes*

- Daytime, nighttime and 24-hour systolic and diastolic BP, evaluated through ambulatory BP monitoring (ABPM);

- Glycosylated hemoglobin (HbA1c), evaluated through blood collection using the high performance liquid chromatography method.

*Secondary outcomes*

- Endothelial function, evaluated by ultrasonography.

- Cardiorespiratory fitness, evaluated through an ergoespirometric test of maximum effort.

- Neuromuscular function, evaluated through chair-stand test, isometric handgrip test, vertical jump, medicine ball throw and balance tests;

- Quality of life, evaluated through the questionnaire WHOQOL-BREF.

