# MATERIAL AND METHODS

# **Study Design**

This is a randomized clinical trial with parallel design in which participants will be allocated to one of two groups: Combined training with two weekly sessions (TC2) and Combined training with four weekly sessions (TC4).

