The sample will consist of 98 participants (49 in each intervention), who will be included according to the above criteria. The sample size calculation was performed considering a minimum difference of 4 mmHg, and dispersion (standard deviation) of ± 10 mmHg in systolic and diastolic BP. A statistical power of 80% and an alpha error of P<0.05 were adopted.

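### The planned 49 participants per arm is half of what the protocol's own inputs require: power for 4 mmHg with SD 10 is about 50%, not 80%

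*Protocol*

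**What the plan says.** The sample-size paragraph at the end of the Protocol's 'Participants recruitment' section gives all its inputs together. The size is "The sample will consist of 98 participants (49 in each intervention), who will be included according to the above criteria". It was calculated "considering a minimum difference of 4 mmHg, and dispersion (standard deviation) of ± 10 mmHg in systolic and diastolic BP". The error rates follow: "A statistical power of 80% and an alpha error of P<0.05 were adopted".

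The comparison to be powered is set elsewhere. Under 'Study Design': "This is a randomized clinical trial with parallel design in which participants will be allocated to one of two groups". Under 'Specific Objectives': "To evaluate and compare the effects of 12 weeks of combined training with different weekly frequencies". Ambulatory systolic and diastolic BP are among the primary outcomes listed there. The randomization section calls for equal group sizes.

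The sample-size paragraph does not name the test or say whether it is one- or two-sided. It does not say whether the SD refers to single readings or to changes, and it gives no correlation between baseline and week 13 and no allowance for loss.

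**The concern.** The number of participants, the difference, the SD, the power and alpha are all stated, so they can be checked against each other. For a comparison of two independent groups they do not agree, and the discrepancy is a factor of two. Because the stated figures contradict one another, this is more than detail that a statistical analysis plan could supply later.

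The power statement shapes how the result will be read. The arms receive the same weekly training volume and differ only in how it is split, so a small or null difference is a realistic outcome. A reader who trusts 80% power may take a non-significant result as showing that two and four sessions work equally well. With 50% power, a true 4 mmHg difference would be missed about half the time, and that reading would have no support.

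**Working it through.** **Inputs (Protocol, 'Participants recruitment').** Difference 4 mmHg; SD 10 mmHg; power 80% (z = 0.842); alpha 0.05, taken as two-sided (z = 1.960); 49 per arm, equal allocation.

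**1. Can the protocol's figure be reproduced?** The two-sample formula is n per arm = 2 × (1.960 + 0.842)² × (10/4)².
- (1.960 + 0.842)² ≈ 7.849 and (10/4)² = 6.25.
- n per arm = 2 × 7.849 × 6.25 = 98.1, so 99 per arm (198 in total).
- The t-test gives 99.1, so 100 per arm (200 in total).

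The stated 49 per arm is not reproduced. Two routes do lead to the printed numbers:
- 98.1 is the number required *per arm*, and the protocol has 98 as the *total*.
- The one-sample (within-arm, before–after) formula gives 7.849 × 6.25 = 49.06, the printed number per arm.

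Neither gives a valid size for comparing two arms.

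**2. Power at 49 per arm.** SE = 10 × √(2/49) = 2.02 mmHg, and 4/2.02 = 1.98.
- Two-sided: 50.0% (t-test); 50.8% (normal approximation).
- One-sided alpha 0.05: 62.6% (t-test). This would still need 78 per arm.

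**3. What 49 per arm can deliver.**
- Difference detectable with 80% power: 5.72 mmHg (t-test).
- 95% confidence interval half-width: t(0.975, 96 df) × 2.02 = 4.01 mmHg.
- SD at which 4 mmHg would have 80% power: 10 × 4/5.72 ≈ 7.0 mmHg.

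**4. Could a baseline correlation r rescue it?** Suppose SD 10 describes single readings. The effective SD is then 10 × √(2(1 − r)) for change scores and 10 × √(1 − r²) for a baseline-adjusted analysis. Every r below is an assumption, since the document gives none. Power is for a two-sided t-test at 49 per arm.

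| r | Change scores | Baseline-adjusted |
| --- | --- | --- |
| 0.5 | 50% | 62% |
| 0.6 | 59% | 69% |
| 0.7 | 72% | 78% |
| 0.75 | 79% | 84% |

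Power of 80% needs r of about 0.755 with change scores and about 0.715 with baseline adjustment. If SD 10 is instead the SD of change, a change-score comparison stays at 50%.

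**5. Loss of participants.** The protocol gives no rate, so these are illustrations at SD 10.

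| Assumed loss | Per arm | Power | Detectable with 80% power |
| --- | --- | --- | --- |
| none | 49 | 50% | 5.7 mmHg |
| 15% | 42 | 44% | 6.2 mmHg |
| 20% | 39 | 41% | 6.4 mmHg |

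**The case against.** The strongest defence is that the paragraph names no test. It attaches the SD to BP itself, which may mean single readings, and the 'Statistical analysis' section plans GEE over time points and groups. With SD 10 per reading and r = 0.75, the variance of a change is 10² × 2 × (1 − 0.75) = 50. The between-arm formula then gives 2 × 7.849 × 50/16 = 49.06 per arm, almost exactly the printed number. So there is a possible origin that does compare the two arms, and the cause of the discrepancy cannot be proved from the text. That much stands. It does not rescue the statement, because the protocol gives no correlation and does not link the GEE analysis to the sample size.

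It is also fair that the objectives cover evaluating as well as comparing, and that 49 suits a within-arm change. That still leaves the between-arm comparison, which is the reason for randomizing, underpowered.

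Two further points limit the remedy and the extras. The more favourable correlation figures belong to a baseline-adjusted analysis. The GEE as described names no baseline covariate, so its time-by-group contrast follows the change-score column. And the loss rates are assumptions: the planned intention-to-treat analysis includes everyone randomized, so the attendance exclusions reduce only the per-protocol analysis.

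**Conclusion.** The concern holds. On the protocol's stated inputs, a two-sided comparison of two parallel arms needs 99 to 100 participants per arm. The planned 49 give about 50% power, and 80% is reached only at a difference of 5.7 mmHg. A one-sided test does not close the gap.

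The conclusion assumes an unadjusted comparison with an SD of 10 mmHg for the quantity compared. It would change only if SD 10 refers to single readings and the correlation between baseline and week 13 is at least about 0.755 (change scores) or 0.715 (baseline adjustment). Whether the per-arm number was taken as the total, a within-arm formula was used, or a correlation was left unstated is inference. In each case the power statement cannot stand as written and must be corrected.

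**What to change.** Correct the sample-size paragraph in one of two ways.

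1. **Keep the inputs and state what they give.** For example: 98 participants (49 per arm) give 50% power to detect a between-arm difference of 4 mmHg with an SD of 10 mmHg (two-sided alpha 0.05); the difference detectable with 80% power is 5.7 mmHg.
2. **Base the calculation on the analysis to be used.** Name the test, say that the SD is for single readings, and state and justify the correlation assumed. With baseline adjustment, r of about 0.715 or more keeps 80%, while 0.6 gives 69% and 0.5 gives 62%. These figures apply only if the 'Statistical analysis' section also adopts baseline adjustment. For the GEE time-by-group contrast as now described, the threshold is about 0.755.

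Under either option, give the figures for the number expected to be evaluable. Add one sentence saying that a non-significant result will be read from the 95% confidence interval against 4 mmHg and not as evidence of equal effect.

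The cost is protocol wording and, under the first option, a less favourable power statement. Option 2 also needs a line in the analysis section if baseline adjustment is chosen. Neither option adds participants.

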## Experimental procedures

The procedures of this study will be conducted at the clinical research center of the Hospital de Clínicas de Porto Alegre (PREVER Study Center and Exercise Pathophysiology Laboratory). From a first telephone contact, individuals interested in participating in the study and who are in agreement with the inclusion and exclusion criteria of the study will be received by the responsible researcher. Once the eligibility of the participant has been confirmed and the participant has answered any questions about the procedures that will be adopted, risks and benefits of the study, the participant will sign the TCLE.

## Training programs

The TC2 and TC4 groups will perform the training with progressive intensity and volume, and will perform the same weekly training overload (i.e., minutes per week, series, repetitions, relative intensity and exercises), but will have this overload divided into different weekly frequencies. The training will last 12 weeks, with a total weekly volume of 120 min in the first weeks (weeks 1-6), progressing to 150 min/week in the last weeks (weeks 7-12). Therefore, the groups will differentiate their training exclusively by the number of weekly sessions that will be used to perform this training, with one group performing 2 weekly sessions and the other group 4 weekly sessions.

The first part of the session will consist of the following RE: push-up, squat, unipodal balance, inverted row, calf raise and crunch. The progression in volume will be performed by increasing the number of sets and repetitions. The intensity of the effort will be adjusted from the range of movement of the exercises, speed of execution, and variations in the number of supports to stabilize the exercises. Individuals must perform 1-4 series of 10-15 repetitions with the load corresponding to 60-70% of 1RM monitored through rating of perceived exertion (RPE), monitored through the CR10 scale. An interval of 90-120 seconds will be adopted between sets and exercises. The second part of the session will consist of AE performed on a treadmill or track and will last 20-50 minutes. The intensity of these sessions will be controlled through the heart rate reserve (HR _reserve_) of the individuals, using intensities between 60-70% of HR _reserve_. In the absence of HR monitors, the stress perception scale corresponding to the above intensities will be used, monitored through the BORG scale with rates of 6-20. In the last session of the week at each 4-week period, after the RE and at the end of each session, information will be recorded regarding the RPE of the participants in the session and the level of enjoyment when conducting the training. It should be noted that the training sessions will always start with the RE, and later on, they will perform the AE, as this seems to be the best order to conduct the training in this population[^41^](#_ENREF_41)^,^ [^42^](#_ENREF_42).

## Evaluations

Before the study begins (week 0) and at the end of the intervention period (week 13), participants will perform evaluations regarding BP, glycated hemoglobin, endothelial function, fitness level, and quality of life. Divided into 3 visits with 24-72h intervals between visits, the different evaluations aim to verify the possible effects of the different interventions on the outcome variables of the study. A food record will be used to characterize eating behavior and to evaluate a possible interference of eating with training responses. The subjects will be recommended not to change their eating habits during the study period.

In the first visit, after signing the TCLE, an anamnesis will be performed to characterize the sample, collection of anthropometric measurements through measures of height and body mass, performed from a stadiometer and an analog balance scale (brand FILIZOLA, BRAZIL). With these values their body mass indexes (BMI) will be calculated, according to the equation mass (kg)/height(m)². A questionnaire will also be carried out to evaluate the quality of life of the participants (WHOQOL-BREF). Also in this session, BP measurements will be performed (after 20 minutes of rest) followed by a familiarization with the exercises that will be used in strength and muscle power tests and with the mask that will be used in gas collection during the cardiopulmonary test.

In the second visit, new BP measures will be performed and the endothelial function evaluation conducted through flow-mediated dilation analysis. The resting electrocardiogram and blood collection will also be performed for analysis of glycated hemoglobin levels. From this blood collection, a sample will be used for analysis of total cholesterol, HDL-c, LDL-c, VLDL-c, which will serve to characterize the sample. Afterwards, the ambulatory blood pressure monitoring equipment (ABPM) will be placed. After 24h of the second visit, each patient must return to the laboratory to remove the ABPM.

On the third visit, after ABPM removal, the evaluation of strength and muscle power tests will be conducted, as well as the cardiorespiratory and unipodal balance evaluation. First the strength, power and unipodal equilibrium tests will be conducted, and after a 10-minute rest, the cardiopulmonary test will be conducted.

*Blood pressure measurement*

Blood pressure during the collection period in the laboratory will be evaluated according to the measurement protocol of the hypertension guidelines of the Brazilian Society of Hypertension and the Brazilian Society of Nephrology. Through these measurements the values of systolic BP, diastolic BP and mean BP will be obtained by the automatic oscillometric method (Dinamap, Critikon, USA). The results of this study will have measures that will be without subjectivity of the operator (operator-independent).

The ABPM, characterized by the periodic measurement of BP in an environment of daily activities, will be performed by portable automatic oscillometric device (ABP 2400, Mortara, Milwaukee, USA). The participants will receive verbal orientations regarding the execution of the exam (operation of the device, measurement position, daily activities). After the end of each experimental session, the cuff of the ABPM device will be placed in the non-dominant arm,, configured to perform the measurement of the daytime every 15 min, and nighttime every 20 min. The waking period will be considered from 6:00 A.M. to 22:59 P.M. and the nighttime period from 11:00 P.M. to 5:59 A.M. All participants will have the beginning of the monitoring scheduled for the same time.

*Glycosylated hemoglobin*

For chronic glycemic data collections, a blood sample will be assessed to evaluate glycosylated hemoglobin (HbA1c) levels with high-performance liquid chromatography method (Bio-rad VARIANT II TURBO System, São Paulo, Brazil).

*Endothelial function*

Flow-mediated dilatation (FMD) of brachial artery will be performed by high resolution ultrasonography (HD7XE, Phillips, USA) in combination with a vascular Doppler (to obtain the flow velocity), through a high frequency transducer (3-12MHz). The evaluation of the FMD will be obtained in a room with low luminosity, controlled temperature and after 15 minutes of lying down. After an arterial occlusion maneuver for 5 minutes, the diameter will be evaluated for 120 seconds and variations will be relativized to the pre-occlusion diameter.

*Cardiorespiratory fitness*

Participants will submitted to maximum pre- and post-training tests to measure maximum oxygen consumption (VO_2máx_). The tests will be performed on ergometric treadmill with mask and gas analyzers, which will be previously connected and calibrated in order to avoid any kind of setback. A 10200 ATL treadmill model from IMBRAMED (Porto Alegre, Brazil) will be used to perform the test, with speed and incline resolution of 0.1km.h^-1^ and 1%, respectively. First it will be heated for 3 minutes and the speed will be slowly increased until it reaches 3 km/h. Soon after, the test will begin at 3-4 km/h and 1% incline, with speed increases of 0.5 km/h every 30 seconds and 1% incline every two minutes. The test will be stopped when the participant indicates their exhaustion by a manual signal. During the tests, participants will be supervised by an experient physician and a researcher. Respiratory gases will be collected through the portable box-type gas analyzer (VO2000, MedGraphics, Ann Arbor, USA).

*Neuromuscular function*

Muscular strength will be assessed through chair-stand test (lower-limbs) and isometric handgrip test (upper-limbs). Isometric handgrip test was chosen because of the great external validity of this evaluation and the association between strength levels obtained in this evaluation and mortality of the population[^28^](#_ENREF_28). Isometric handgrip strength will be measured in both arms with an analogic hand dynamometer (Jamar Sammons Preston Rolyan, Bolingbrook, IL, USA). The participant will remain seated with upright posture, placing the forearm parallel to the ground (elbow flexed at 90°). Thereafter, the participant will be instructed to perform a maximal hand squeezing contraction with sustained (isometric) effort lasting 5-s. Three attempts will be performed in each hand with 30-s rest intervals. The medicine ball throwing test will be performed by 3 attempts with 20 seconds of interval. For this test, a medicine ball of 1 kg for women and 2 kg for men will be used. From a 90 degree bent shoulders position, the participant will throw the ball as far as possible, performing the movement at maximum speed in order to increase the efficiency of the stretching and shortening cycle.

To evaluate the strength and muscle power of the lower limbs will be used the chair-stand test and the countermovement jump test (CMJ), respectively. The evaluation of the muscle power of the lower limbs will be obtained through the height of the CMJ monitored through a software (My Jump 2)^43^. Before starting the data collection the subjects will perform a warm-up that will also serve as a familiarization for the test, performing 3-5 jumps. The subjects will start from the orthostatic position, with their hands on the waist, perform a squat and then the flight phase. For the correct execution of the test, participants will be instructed to keep their hands on their waist throughout the test, perform the transition phase between crouching and the flight phase quickly, jump as high as possible and land at the same starting point. During the test, 3 CMJ jumps will be performed with a 20 second interval between each jump. The strength evaluation of the lower limbs will be obtained by performing the maximum number of stands that the participants can perform for 30 seconds. In addition, the time (seconds) that participants take to perform the first five stands will be counted. The test will start with the participant seated in the chair, the back should not be supported in the stands. Feet should be shoulder-width apart and fully supported on the ground. The upper limbs are crossed at the level of the wrists and against the chest. At the "start" sign, the participant rises to the maximum extension (vertical position) and returns to the initial seated position.

*Quality of life assessment*

The WHOQOL-BREF questionnaire, a version translated and validated in Brazil, will be used to evaluate the quality of life. The questionnaire contains 26 questions and is divided into four domains (physical, psychological, social and enviromental). The answers follow a Likert scale (1 to 5, the higher the score the better the quality of life) and the values of each domain will be expressed in percentage values.

## Randomization and allocation concealment

For the randomization of participants in the different experimental groups (TC2 and TC4), stratified and block randomization will be used. The strata will consist of two age groups (50-65 and 65-80 years). Thus, the participants in the different age groups will be distributed in a balanced way by age stratum and randomly among the different interventions. In addition, participant distribution blocks will be created among the interventions to ensure that the number of participants in each group is equal.

The subjects and researchers responsible for the interventions will be blinded for the allocation of the interventions and will only have access to this information at the time of randomization. The study will have an epidemiologist responsible only for the randomization and confidentiality of the allocation, not participating in the recruitment, evaluation or intervention with the patients. This researcher will inform through telephone contact with the executing researchers the different sequences of randomization for each research subject. The researcher responsible for the statistical analysis of the study outcome variables will also be blinded by different codes for each type of intervention. The randomization process will be performed in online software ([randomization.com](http://www.randomization.com)).

In case of an availability of participants larger than the necessary number will be invited the first participants who get in touch and fulfill all the prerequisites for participation in the study. On the other hand, if availability is lower than that of eligible participants, dissemination of the project will continue until this necessary sample number is reached.

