## Statistical analysis

Shapiro-Wilk and Levene tests will be used for data normality and variance homogeneity, respectively. If the data present normal and homogeneous distribution, parametric statistics will be used. Transformations will be performed if the data do not present normal distribution to make them parametric. The Generalized Estimating Equations (GEE) and the Bonferroni post-hoc test will be used for the comparison between the moments and groups/ interventions. In addition, statistical analysis by protocol will be performed, in which those who have presented three consecutive absences in training will be excluded from the analysis, as well as those who obtain a frequency lower than 75% during the period of interventions. Statistical analysis by intention to treat will also be performed, in which all randomized participants will be included in the analyses. The level of significance adopted will be α = 0.05 for all analyses. The statistical package SPSS version 22.0 will be used to perform the statistical procedures.

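### Randomisation is stratified by age group, but the planned GEE names only time and group; as written, its between-arm standard errors are conservative to the extent that age stratum predicts the outcome

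*Protocol*

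**What the plan says.** Under Randomization and allocation concealment, the protocol states that "stratified and block randomization will be used". It defines the strata this way: "The strata will consist of two age groups (50-65 and 65-80 years"). The stated aim is balance between the interventions within each age stratum.

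Under Statistical analysis, it states: "The Generalized Estimating Equations (GEE) and the Bonferroni post-hoc test will be used for the comparison between the moments and groups/ interventions". Time point and group are the only factors named. The section also sets out per-protocol and intention-to-treat analyses, and adds: "The level of significance adopted will be α = 0.05 for all analyses". It neither mentions age or the randomisation stratum nor says that other terms are excluded.

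Measurements are taken at week 0 and week 13 (Evaluations). Ambulatory blood pressure and HbA1c are primary; endothelial function, cardiorespiratory fitness, neuromuscular function and quality of life are secondary (Specific Objectives).

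**The concern.** Stratified, blocked allocation gives the arms nearly the same age mix. Differences in outcome between the strata therefore contribute almost nothing to the sampling variation of the arm difference. A model without the stratum does not know this and counts those differences as residual noise. If the stratum is prognostic, the reported standard error exceeds the true one, confidence intervals are too long, and tests reject less often than their nominal level.

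The protocol gives a reason to think age matters for some outcomes. Its background section describes the decline in muscle function as steeper from about 65 to 70 years, close to where the strata are cut, and several secondary outcomes are tests of strength, power and balance. What is at stake is precision: error bars that do not match the design, and a somewhat greater chance of missing a real difference.

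**Working it through.** **Figures in the protocol.** No age effect, standard error or correlation is stated, so there is no figure on this point to reproduce. The scale comes from the sample size paragraph (Participants recruitment): "considering a minimum difference of 4 mmHg, and dispersion (standard deviation) of ± 10 mmHg in systolic and diastolic BP", "The sample will consist of 98 participants (49 in each intervention"), and 80% power at alpha 0.05. The usual two-group formula, 2 × (10 × (1.960 + 0.842) / 4)², gives 98.1 per arm, so 49 per arm is not reproduced (half that value, 49.06, is the one-sample result). That is a separate matter. Here 49 per arm and SD 10 mmHg only set the scale.

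**Step 1: true level of the unadjusted test.** Let R² be the share of variance of the analysed quantity explained by the stratum (assumed). The true standard error is the reported one times √(1 − R²), so the true two-sided level is 2 × (1 − Φ(1.96 / √(1 − R²))).

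- R² = 1%: 1.96 / 0.995 = 1.970, level 4.9%
- R² = 5%: 1.96 / 0.975 = 2.011, level 4.4%
- R² = 10%: 1.96 / 0.949 = 2.066, level 3.9%

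**Step 2: the same in mmHg, arms compared at one time point.** Assume equal strata with means d apart and total SD 10, so R² = (d/2)² / 100. The unadjusted SE is 10 × √(2/49) = 2.020 mmHg. The adjusted SE is 2.020 × √(1 − R²).

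| Assumed d (mmHg) | R² | Adjusted SE | Unadjusted SE too wide by | Power for 4 mmHg with the term |
|---|---|---|---|---|
| 2 | 1% | 2.010 | 0.5% | 51.2% |
| 4 | 4% | 1.979 | 2.1% | 52.4% |
| 5 | 6.25% | 1.956 | 3.3% | 53.4% |
| 10 | 25% | 1.750 | 15% | 62.8% |

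Power without the term is about 50.8%, taking the SD of 10 at face value.

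**Step 3: the group-by-time contrast.** With two time points and complete data, this contrast is the difference between arms in mean change. A stratum effect that is the same at both visits cancels within each person. In 400 simulated trials per scenario (100 participants, exchangeable GEE with robust SE, SD 10 within stratum, within-person correlation 0.5), adding a stratum main effect left the estimate and its SE unchanged, with differences below 10⁻¹³. In the same model, with a 5 mmHg stratum difference, the SE of the single-time arm comparison fell from 2.04 to 1.97.

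Adding stratum-by-time moved the group-by-time SE as follows:

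- strata 2 mmHg apart in change: 1.989 to 1.966 (about 1%)
- strata 4 mmHg apart in change: 2.018 to 1.970 (about 2.5%)
- no stratum effect at all: 1.976 to 1.968 (about 0.4%)

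The last line shows that roughly 0.4 percentage points of these falls come from fitting extra parameters with an uncorrected robust SE, and are not a real gain. Theory agrees. The variance of change within a stratum is 100 here, and a stratum difference of 2 or 4 adds 1 or 4. The expected reductions are therefore 1 − √(100/101) = 0.5% and 1 − √(100/104) = 1.9%.

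**The case against.** The strongest reply is that the analysis section does not write out a model. It says only that GEE and the post-hoc test "will be used for the comparison between the moments and groups/ interventions", which describes comparisons and is not a full list of terms. Covariates are commonly left to a statistical analysis plan, and one may exist. This stands in part. A reader might infer that the stratum is excluded; the protocol does not say so. It does name the factors, however, and leaves out the one the design uses, so an analyst who follows the text would omit it.

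A second reply is that the loss is assumed and small. This also stands. A reader might take it as fact that the standard errors are too wide. That depends on age stratum predicting the analysed quantity, and the protocol gives no such figure. Its remark on ageing concerns the level of muscle function. It does not concern blood pressure, HbA1c or change with training, and for group-by-time only prediction of change matters.

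Third, a reader might conclude that stratification is wasted, or that adjustment would make the arm effect itself much less variable. Neither follows. The balance is kept whether or not the stratum is modelled. The point estimate and its true variance barely move, and it is mainly the reported standard error that falls.

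Finally, adding the stratum as a single fixed factor might look sufficient. Step 3 shows that it does nothing for the group-by-time contrast with complete data.

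**Conclusion.** The point holds as a modest mismatch between design and analysis. As written, the between-arm analyses are conservative wherever age stratum is prognostic, with a true level of about 4.9% to 3.9% for an assumed R² of 1% to 10%. For blood pressure at a single time point, assumed stratum differences of 2 to 5 mmHg make the standard error 0.5% to 3.3% too wide. For group-by-time, assumed differences in change of 2 to 4 mmHg correspond to about 0.5% to 2%. The loss is probably small for ambulatory blood pressure and HbA1c and larger for week-13 comparisons of fitness and strength.

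The direction is secure. The size rests on assumed age effects, equal strata and complete data. Nothing here implies bias or inflated false positives, and the trial's validity is not in question. The change is worth making because it is free and aligns the analysis with the randomisation.

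**What to change.** In the Statistical analysis section, state that every between-arm GEE, intention to treat and per protocol, includes group, time, group-by-time, age stratum and stratum-by-time. The stratum main effect serves comparisons at one time point; the stratum-by-time term is needed for the group-by-time contrast.

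Define the stratum as the randomisation list from which the participant was actually drawn. Both strata as written include age 65, so the stratum cannot always be rebuilt from recorded age. The epidemiologist who holds the lists can pass the stratum to the blinded analyst without revealing the arm.

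The cost is two model terms (two parameters, with 98 participants) and no new data. The gain is a reported standard error that matches the design.
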